#### 2.3.3 Type of health gain considered

Health gain can be framed as Quality Adjusted Life Years (QALYs), years of life or quality of life. The relative difference in value between child and adult gains may differ based on the type of gain being considered. Ultimately, much HTA in Australia and elsewhere relies upon Incremental Cost Effectiveness Ratios expressed in terms of cost per QALY, hence it would be useful for decision makers to know relative values framed as QALY weights. However, the use of QALYs within a question would require the respondents to understand this concept. This is likely to be an additional comprehension challenge and add to responder burden. If wishing to consider potential differences in QALYs gained through life extension and QALYs gained through quality of life improvements, then this distinction would need to be included in addition to the QALYs, i.e. a gain of 1 QALY derived from a quality of life improvement. Likewise, if different types of quality of life improvements have different relative weights, this also needs to be considered. For simplicity, the PTO questions in this study will consider improvements in length of life (spent in full health) only and quality of life only.

#### 2.3.4 Number of years of life extension

Previous PTO studies using additional years of life consider gains from 1 year [39] up to 40 years [26]. When wanting to understand the value of extending life, it is impossible to avoid the fact that this is only relevant when an individual is close to death and yet, ideally, we would prefer to avoid ‘end of life’ considerations which might incorporate other values which interact with age [40] (for example, adults might be perceived as needing time to get their affairs in order; young people may be perceived as needing time for parents to emotionally prepare for their death). This would suggest a preference for using a longer time-period within the PTO questions.

Some surveys have tried to frame the question through spending time in a coma or being bed-ridden [36], thereby valuing the time spent during a particular age but avoiding the considerations around death. Another option is to suggest that patients may be eligible for future funding [20], however, this raises an additional uncertainty in terms of what respondents actually consider relating to this unknown future outcome.

A particular challenge with years of life gain in our context is the changing age of the groups during the period of the years of life gain; a 10-year gain for a 5-year-old versus a 20-year-old, for example, moves towards trading between a 15-year-old versus a 30-year-old. Holding the patient age in years constant would require a period below 1 year (i.e. the patient was aged 10 at the point of the decision and the additional extension of their life is below 12 months so that they remain aged 10 throughout that period), which also has the benefit of being a marginal health gain as preferred in decision making (see above). These two considerations (avoiding treatment gains occurring at the end of life and avoiding treatment gains during which the patient groups get older) conflict with each other. Ease of interpretation for respondents is an additional consideration, which favours using whole years.

In this study, we will ask questions using two different life extensions (2 and 5 years) to test the difference this makes to preferences. These time lengths were chosen to limit the potential for responses to be heavily influenced by being close to death, whilst also limiting the potential variability in interpretation of the age of the groups and generating values for reasonably marginal health gains.

#### 2.3.5 Choice of quality of life domain

The quality of life loss which is averted by the hypothetical treatment in the PTO question could cover any aspect or domain of health-related quality of life or could be described in terms of a generic percentage loss in overall quality of life. There may be some dimensions of quality of life in which the relative value of improvements in that dimension for a child versus adolescent versus adult may differ e.g. the importance of being able to manage personal care.

The quality of life domains for our study PTO questions needed to be relevant across all ages that are to be included in the study (some aspects of quality of life may be unique to adulthood e.g. aspects of independent self-care). The domains also need to be easily described and understood. Given the potential for age-based prioritisation to differ across different types of health loss, the study includes mental health and two different types of physical health. Specifically, health states include:

‘Distress (low mood and anxiety)’. This is chosen as a common mental health problem. The choice of term ‘distress’ is chosen as this can be applied across all age groups including infants.‘Problems walking or moving about’. We chose to include the term ‘moving about’ in addition to ‘problems walking’ as alone this is not appropriate to describe health loss in a 1-month-old.‘Pain’. We chose to include pain as this is a common health problem experienced across the age range and is the dimension often judged by the public to be most important in health state valuation studies.

We acknowledge that there may be asymmetry in the value function by age when considering health gain versus health loss; however, exploring this is beyond the remit of this study.

#### 2.3.6 Without-treatment counterfactual and remainder of life course

PTO questions which involve an extension of life are also questions about delaying death. Typically, no benefit can be experienced by the groups beyond the end of treatment and the questions are framed such that death occurs immediately after the treatment period. As noted above, some studies have tried to find a way of patients’ life continuing after the life extension period by asking about patients avoiding being in a coma (during which they would gain no valuable experience from their life making it broadly equivalent to being dead). However, this raises additional issues and complexity e.g. introducing implications for parents/families, which may affect results but which would not arise in most treatments which extend life.

For quality of life improvements, death does not need to follow the period of health gain (compare Fig 2 with Fig 1). If the period of health gain is followed by additional years of life, there is a risk that respondents will think about differences in future potential health impacts by age and ignore the given information that the health gain between the two age groups is intended to be exactly the same. Respondents may, for example, prefer to treat younger patients if they think the treatment will avoid long term health implications. This raises two concerns; firstly, the comparison between the relative weights derived from quality of life gain and life extension gain is problematic if they are not comparing like for like. Secondly, the age-weights may be biased if respondents do not interpret the health gain to patient groups as the same thing.

**Fig 1 pone.0302886.g001:**
[figure not shown]
A life extension for 2 years for a 5-year-old versus a 40-year-old after which time they will die or require additional funding (blue shading is the treatment gain being considered, without treatment patients would die at age 5 or 40, the black line is the health profile with treatment).

**Fig 2 pone.0302886.g002:**
[figure not shown]
Quality of life deficit for two years for a 5-year-old versus a 40-year-old after which time they die (blue shading is the treatment gain being considered, without treatment patients would incur a drop in their HRQoL, the black line is the health profile with treatment).

These concerns could be addressed if the quality of life improvement was followed by death (see Fig 2). However, given the potential for the closeness of death to impact upon respondent preferences, if most health interventions to increase quality of life are not targeted at the end-of-life period then framing the treatment period as being followed by death may limit the generalizability of the age-weights. If death does not follow the enhanced quality of life period, then questions must be framed as either returning to full health (Fig 3) or remaining (or returning) to below full health level (Fig 4). The duration of the treatment quality of life gain could adopt any number of years, but a longer duration will change the age of the patient group.

**Fig 3 pone.0302886.g003:**
[figure not shown]
Quality of life deficit for two years for a 5-year-old versus a 40-year-old after which time they return to full health for specified life expectancy (blue shading is the treatment gain being considered, without treatment patients would incur a short-term drop in their HRQoL, the black line is the health profile with treatment).

**Fig 4 pone.0302886.g004:**
[figure not shown]
Quality of life deficit for two years for a 5-year-old versus a 40-year-old after which time they return to the level of quality of life they would be at without treatment (blue shading is the treatment gain being considered, the black line is the health profile with treatment).

Given the potential challenges of interpretation with other framings, the study PTO questions about treatments extending years of life will be followed by death. PTO questions about treatments temporarily improving quality of life will be over a period of 2 years with the patients returning to full health after that period; for example, the health gain is described as a treatment which ‘*Prevents a 2-year illness with the symptom distress (low mood and anxiety) after which they would return to normal health with no long-term health consequence*’.

#### 2.3.7 Group ages

In choosing the ages of children and adults for comparison within the PTO questions several factors were considered, including ease of interpretation, feasible sample size for each age comparison and existing gaps in the literature. The age category ‘newborn’ is often used in studies exploring social value, but this may be a slightly ambiguous category since a small baby a few months old could be described as newborn, as could a baby a few minutes old. A common childhood age used in the literature is 10 years old, therefore including this category would enable a direct comparison of findings. The recent systematic review [11] identified gaps in the evidence base in relation to very young children (<5 years) and young adults (18–24 years). It also identified a non-linear relationship between age and social value (lower for the very young children and adolescents compared with primary school age children) which suggests there would be a benefit to including many different young ages within the study.

The study adopts thirteen age categories (1 month, 2, 4, 6, 8, 10, 12, 14, 16, 18, 20, 22 and 24 years) enabling a reasonable number of respondents answering questions on each age category whilst including sufficient age categories to identify the hypothesised non-linearity of the value of health gain across different ages. The study also seeks to understand the relative preferences held towards health gains for patients as they transition from childhood to adulthood, hence three young adult age categories are also included.

To ensure a reasonable sample size for each age comparison (given the fixed study budget), only two adult ages were used in the main questions (with two other child/youth ages used in the chaining questions). We chose adult ages which would unambiguously be considered ‘adulthood’ but would not evoke issues around health and healthcare in older ages, hence pick up a potential preference to dis-favour very old adults compared to younger adults. In piloting, some respondents prioritised 40 year olds over children due to an assumption that they may have young children as dependents, therefore we complemented this age with an older age, 55 years, which is less likely to be associated with parents of small children.

The social value of health gain to young and middle-age adults versus old adults is outside the scope of this study.

#### 2.3.8 Choice of group size in terms of number of patients

Common group sizes used in PTO studies are 10 or 100. A potential concern within PTO studies is that responders may consider the absolute difference between the number of people within each option of a PTO as well as ratio differences resulting in different ratios depending upon initial group size. The smaller absolute size may lead to greater risk of absolute differences impacting responses as the decision may feel more personal with fewer patients. Petrou et al., (2013) [9] tested the impact of a PTO with 1000 versus 100 patients and found this to have minimal impact upon the estimated weights.

PTO questions are at risk of start point bias [41]. An option commonly used to address and test for this is to randomly adopt different starting points. Unlike when using the method to compare different types of health gain (i.e. to estimate social utility values), when comparing different ages there is a policy default option that gains are of equal value therefore anchoring bias of equal value is a reasonable position.

This study adopts a starting point for the PTO questions of 100 patients in both groups. This is an easy number for respondents to work with and maintains more statistical anonymity than using 10 patients. The starting point bias will therefore be in favour of equity.

#### 2.3.9 Process for reaching equivalence

In choosing the process for reaching equivalence, considerations include whether to allow the respondent to express equivalence in any of the questions, and the size of the groups to be shown to respondents.

It is common within the literature to require respondents to express a preference between patient groups in a PTO question (e.g. Baker et al., 2010 [28], Petrou et al, 2013 [9]). Forcing participants to decide which group should receive treatment has been seen as a means of ensuring respondent engagement. Damschroder and colleagues note that if a respondent states that the treatment options are equivalent this might mean that they hold them to have equal value, but it could also mean that they think *“the kinds of choices presented by the PTO should not ever be made*. *Alternatively*, *the subject may not understand the task or may not have taken the task seriously and simply took the quickest path through the survey*.” [42](p 173). Nord et al noted, “*It would not be surprising if some avoided the issue simply by maintaining that all patients should be equally entitled to treatment*, *even if this is not possible in the real world*. *To the extent that this occurs*, *public responses to person-trade-off questions will not be of very great help in decision making about resource allocation*” [24](p 207).

However, holding a view of no preference between treating patient groups of the same size yet different ages is a legitimate preference. Given the potential impact of focusing effects, encouraging respondents to commit to a preference for one age group in the first question may impact upon responses to later questions and thus overall results. The current literature does not have sufficient comparable studies to explore this, hence the full impact of removing an option of equivalence when group sizes are equal is unknown. This PTO will incorporate a methodological test on the impact of allowing respondents to express indifference between age groups. Respondents will be randomised to either be given the opportunity to express no preference or be forced to choose between the two options. Through the qualitative work and comparisons to other parts of the survey we will try to discern whether respondents who opt for equivalence are:

trying to find the quickest way out of the studyavoiding making a decision because it is unpleasant to do soavoiding making a decision because it is too difficult and they feel unable toexpressing a genuine preference of equivalencefailing to understand the question

To counter respondents learning that selecting the equivalence option is a quick way to progress through the survey, we will display an additional question when equivalence is chosen at the first question in which group sizes are both 100. This will always show group sizes of 100 versus 75 and therefore also acts as a potential consistency check to help identify genuine preferences.

As part of the process of moving to equivalence, a decision is required on which group size to vary; always the same patient group (e.g. always children), the preferred group, or the least preferred group. If respondents hold different views on which group represents the most valuable health gain, then always holding the same patient group at 100 patients will result in some equivalence values being above 100 and some below 100. When the patient group for the preferred option is reduced in size, this is naturally bounded by the size of the group, i.e. it cannot go below one patient. However, when the patient size of the least preferred group is allowed to vary, this will increase and have no natural upper limit.

In this study, the questions following the initial choice will depend upon respondents’ answers, with the least preferred group from the initial choice always remaining at 100 patients. For example, if participants prefer Program A, then this patient group size will be reduced in size. Thus, we will be able to avoid very extreme values as the lowest ratio is 1:100.

Some equivalence studies ask respondents to directly state the equivalence values; however, where this has been piloted in other studies, it has generally been perceived as problematic and difficult for responders (e.g. Al-Janabi et al, 2022 [43]). An alternative approach (drawing upon best practice for willingness to pay studies) is to present a single PTO question with a range of different group sizes (e.g. Eisenberg et al, 2011 [44]), although this limits the data that is provided. A more common approach is to iteratively move towards equivalence through a number of follow-on questions. The number of iterative questions used in PTO questions is typically around 4 (e.g. Reckers-Droog 2019 [37], Al-Janabi et al, 2022 [43]) to 6 (e.g. Petrou et al, 2013 [9]), although some studies, particularly those with interviewers, use as many as it takes to reach equivalence. Equivalence can be reached by the ‘ping-pong’ method (oscillating up and down in terms of relative group size), a gradual increase or decrease of one group size (‘titration’), or bisection which involves halving one group size initially, and for follow-on questions depending upon the previous response, either halving the group size again or using the midpoint between the two group sizes from the previous question or between the preferred group size from the previous two questions.

The ‘ping-pong’ search approach has an advantage of minimising the starting point bias [24]; however, in this case the starting point of 100 patients in each group is a defensible default position; therefore, starting point bias is less of a concern. The ‘ping-pong’ method can be confusing for respondents and has been found to take longer and have higher standard deviation than titration in standard gamble health valuation studies [45].

A bisection approach was chosen for this study with three or four follow-on questions, with the number of patients in the preferred group initially halved (to 50). Follow-on questions iterate towards the indifference point by roughly halving the remaining range of uncertainty but using numbers which are easy for the respondent to process (e.g. rounded to the nearest ten or five patients). The number of patients within each question is shown in the flow chart (Fig 5) below. Our use of four (or for some choices five) iterative questions seeks to achieve a balance between the likely number of subsequent questions required prior to reaching equivalence, the survey duration, ease of comprehension and avoiding boredom for responders.

**Fig 5 pone.0302886.g005:**
[figure not shown]
PTO iterations of the question flow showing number of patients in Program A vs Program B.

#### 2.3.10 Supporting the comprehension of respondents

Given that the purpose of PTO studies is to inform healthcare policy, it is important that respondents understand the questions they are being asked and the implications arising from their answers. One option to support respondent understanding could be to show the aggregate health gain comparison implicit in the respondents’ decision and ask for confirmation–thereby aiming to make the lower health gain in the preferred group implicit in the trade off choice more salient. For example–if the respondent opts for 50 young people over 100 older people and the health gain is 2 years life extension they could be asked “That would mean that you would prefer treatments giving 100 years of additional life to patients aged X than an identically costing treatment which gave 200 years of additional life to patients aged Y–are you happy with that choice?” This could be included in the initial questions to both increase respondent understanding and to improve confidence in the respondents’ choices. However, there are some problems with this:

Quality of life improvements over time can only be aggregated to QALY gain if they are expressed as a percentage of full quality of life (e.g. on a VAS scale)If an opportunity for respondents to change their minds is included in some questions but not all, then a direct comparison between questions with and without this option is no longer possible.It introduces additional complexity and time for the respondent.A feedback check which states the years of life lost arising from the choice frames the choice within a utilitarian framing. This might then influence respondent’s subsequent preferences.

Several previous PTO studies have used a ranking exercise in part as a warmup (e.g. Petrou et al, 2013 [9]) and in part as an internal consistency comparison. Whilst ranking data may provide a useful comparison, it does not provide a warmup of the same style as subsequent questions within a PTO survey and can take a considerable time.

Several steps will be taken in this study to support good understanding of the survey by responders. This includes extensive testing and piloting of the survey, including a mandatory introductory video to help respondents understand the purpose and how to answer questions and including a ‘back’ button to enable responders to change previous answers where they may have made an accidental mistake.

#### 2.3.11 Testing data quality and the stability of preferences

Internal consistency of responses can be assessed by tests of cardinal transitivity [46], which is also referred to as ratio consistency, multiplicative transitivity or triad consistency. An individual’s PTO equivalence value for ages 10 versus 20 and 20 versus 30, for example, should accurately predict their PTO equivalence value for age 10 versus age 30. To test this at an individual level requires individuals to be asked at least three questions which ‘chain’ together.

Internal consistency may be judged by comparing PTO answers against other methods for eliciting aged-based preferences such as opinion questions and ranking. However, past evidence suggests fairly systematic differences across research methods with ranking more often being linearly related to age, and opinion surveys responses more likely to reflect a preference for equal treatment [11]. Therefore, these indirect comparisons cannot say much about data quality.

This survey will include an attention check question, consistency comparisons to screening data based on personal demographic data and a minimum time to complete, all of which aim to exclude responders who are not engaged with the survey. We will also consider consistency comparisons to attitudinal questions, but these will not be treated as strict quality checks since there may be legitimate reasons for these differences.

A ratio test will be undertaken for one of the years of life extension questions by chaining PTO values. Each respondent will answer the main PTO questions for just one age. For the question relating to life extension of 2 years they will answer two additional chaining questions i) their given age compared to an age which is either higher or lower by 10 years, as shown in Table 1A, and ii) this age compared to aged (40 or 55), as shown in Table 1B. The expected PTO value will be calculated for each individual based on the two PTO equivalence values (Age X vs (40 or 55)) x (Age Y vs (40 or 55)) and this will be compared to the actual equivalence value (Youngest from X or Y vs (40 or 55)). For example, if the respondent is given age 8 for their PTO questions, they will be asked to complete a PTO comparing patients of ages 8 vs (40 or 55). They will also be asked to compare ages 8 vs 18 and ages 18 vs (40 or 55). The product of the last two responses (the expected value) will be compared to the ages 8 vs (40 or 55) response (the actual value).

**Table 1 pone.0302886.t001:** a. A given age compared to an age either higher or lower by 10 years. b. Age Y (values from Table 1a) compared to age (40 or 55).

Age		Ages used in the PTO for life extension of 2 years		
X		Randomly chosen from one of 13 ages (1 month to 24)		
Y		Age X plus 10 years if X < = 12 OR Age X minus 10 years if X > = 14		
	Expected value		Actual value	
If X is the youngest age	(Age X vs Y) x (Age Y vs (40 or 55))		X vs (40 or 55)	
If Y is the youngest age	(Age Y to X) x (Age X to (40 or 55))		Y vs (40 or 55)	

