We will explore the uncertainty around the ROM and MOIR using bootstrapping of the pairs of assigned values described above. We will use 1000 replications with replacement to calculate the percentile confidence interval (CI 2.5%, 97.5%). Other approaches will be explored depending upon the skew of the bootstrap data.

The data collected alongside the qualitative interviews will be combined with the main dataset.

Results of the test of chaining of responses will be considered by comparing the predicted equivalence value (from the chained PTOs e.g. age 2 vs age 12 and age 12 vs age 40) to the related actual equivalence value (e.g. age 2 vs age 40). The predicted (from chained PTO questions, see Table 1A) and actual values will be shown in a scatter plot. We will categorise respondents into meeting or not meeting the chaining test based on whether they display a preference reversal or if the estimate equivalence group size and the actual group size have a difference of 20 or more people (alternative thresholds will be considered). We will use logit regression to explore whether not meeting the chaining test is related to respondent characteristics or other indicators of data quality.

For each age comparison, we will report ratio of the means and median of the individual ratios, for the 5 health contexts. T-tests will be used to determine if the mean of the ratios is statistically significant different between two study arms (offering a choice of equivalence vs not offering the choice of equivalence), and Wilcoxon’s U-test will be used to determine if median values are statistically significantly different between two arms. An example of how the data will be presented is shown in S4 Table. T-tests will be used to determine if the mean of the ratios value is statistically significantly different between two contexts comparing a health gain of 5 years versus 2 years, and Wilcoxon’s U-test will be used to determine if median values are statistically significantly different. Kruskal-Wallis H tests will be used to determine if the ratios are statistically significantly different between the three contexts across relieving pain, mobility problems and emotional problems.

We will produce histograms showing the distribution of equivalence values for each age comparison; combined, and separately for the forced (dichotomous) and unforced (offering equivalence choice) modes.

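### Chaining test: one sentence in 2.3.11 prints a product that is not a chain, and the 20-person fail rule in 2.7.3 is uneven for a multiplicative property

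*Protocol article*

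**What the plan says.** Each respondent has an assigned age X. For the 2-year life extension they also answer for an age Y ten years older or younger (section 2.3.11 and Table 1), which gives three answers: X versus Y, X versus the adult, and Y versus the adult.

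The protocol article states the expected value in four places:

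- Section 2.3.11, formula sentence: "Age X vs (40 or 55)) x (Age Y vs (40 or 55)) and this will be compared to the actual equivalence value", the actual value being that of the younger of X and Y against the adult.
- Section 2.3.11, worked example for age 8, which adds the questions 8 against 18 and 18 against the adult: "The product of the last two responses (the expected value) will be compared to the ages 8 vs (40 or 55) response".
- Table 1, when X is the younger: "Age X vs Y) x (Age Y vs (40 or 55")). The row for Y as the younger has the same structure.
- Section 2.7.3: the prediction comes "from the chained PTOs e.g. age 2 vs age 12 and age 12 vs age 40", set against age 2 versus age 40.

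Section 2.7.3 gives two grounds for failing. One is a reversal in the direction of preference. The other is a gap on the group-size scale, which applies "if the estimate equivalence group size and the actual group size have a difference of 20 or more people (alternative thresholds will be considered"). A logit regression then relates failure to respondent characteristics and other data-quality indicators. Table 2 supplies the group sizes: banded answers take the mid-point, and anyone who still prefers 1 patient to 100 is assigned 0.5.

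**The concern.** Two things look wrong.

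First, the formula sentence multiplies two answers that are both against the adult. The X-versus-Y answer, which is needed to link them, never enters, and the direct answer being predicted appears inside its own prediction. Code written from that sentence would not test transitivity.

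Second, section 2.3.11 presents this as a ratio test, but the pass rule is an absolute gap in people. A gap of 20 people is a small ratio error near 100 and a very large one near 1.

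At stake is Aim 4 in Box 1. Section 2.7.5 sets test-retest aside, and section 2.3.11 says comparison with opinion and ranking questions says little about data quality. Chaining is therefore the main individual-level evidence of consistency. If passing depends on how strongly a respondent favours one age group, the pass rate and the logit partly describe preference strength.

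**Working it through.** **Inputs.** Group sizes and bands are from Table 2. The less preferred group is always 100 (section 2.3.9). The 20-person and reversal rules are from section 2.7.3. The Table 2 weights reproduce as 100/size (100/0.5 = 200, 100/5.5 = 18.18, 100/17.5 = 5.71), except that 100/32.5 = 3.077 is printed truncated as 3.07.

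**1. The printed product.** Whichever of X and Y is younger, the printed product equals the direct answer multiplied by the middle age's answer against the adult. It matches the direct answer only if the middle age and the adult are valued equally. Take a perfectly transitive respondent who values X and Y equally and treats 50 of either as equal to 100 adults (equivalence option offered):

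- Printed product: 100 × 0.50 × 0.50 = 25, against an actual 50. The gap is 25, so they fail.
- Table 1 product: 100 × 1.00 × 0.50 = 50, against an actual 50. The gap is 0, so they pass.

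**2. The 20-person rule with the Table 1 product.** Let a respondent give the same pro-younger answer g to all three questions. The predicted size is g²/100, the gap is g − g²/100, and the ratio error is g ÷ (g²/100) = 100/g. There is no preference reversal.

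| g | Predicted | Gap | Fold error | Result |
|---|---|---|---|---|
| 0.5 | 0.0025 | 0.4975 | 200 | passes |
| 5.5 | 0.30 | 5.2 | 18.2 | passes |
| 17.5 | 3.06 | 14.4 | 5.7 | passes |
| 25 | 6.25 | 18.75 | 4.0 | passes |
| 32.5 | 10.6 | 21.9 | 3.1 | fails |
| 45 | 20.25 | 24.75 | 2.2 | fails |
| 50 | 25 | 25 | 2.0 | fails |
| 55 | 30.25 | 24.75 | 1.8 | fails |
| 67.5 | 45.6 | 21.9 | 1.5 | fails |
| 82.5 | 68.1 | 14.4 | 1.2 | passes |

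**3. Would another threshold help?** The gap equals g(100 − g)/100, which is symmetric about 50. Any cut-off that flags g also flags 100 − g. A cut-off low enough to flag g = 5.5 (18-fold) would also flag 94.5, where the error is 100/94.5 = 1.06-fold.

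**4. Do transitive respondents fail under the Table 1 product?** Exactly transitive respondents were passed through the Table 2 bands, with 150,000 uniform random draws per scenario (an assumption, so shares are illustrative).

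- *Both links favour the younger group:* none fail. The largest gap is 17.5 in the forced arm and 14.4 in the unforced arm.
- *The links point in opposite directions:* about 4.6% fail. Example: indifference at 26 of X to 100 of Y, and at 39 adults to 100 of Y. The true X-versus-adult weight is (100/26) × 0.39 = 1.5, a size of 66.7, banded to 67.5. Both links are banded to 32.5, so the prediction is (100/32.5) × 0.325 = 1, a size of 100. The gap is 32.5, so they fail. The cause is the mid-point banding.

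**5. Interval overlap on the same cases.**

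- g = 17.5 (band 10 to 25): chained interval 1 to 6.25, no overlap with 10 to 25, so inconsistent.
- g = 67.5 (band 60 to 75): chained interval 36 to 56.25, no overlap, so inconsistent.
- g = 82.5 (band 75 to 90): chained interval 56.25 to 81, overlaps, so consistent.
- Mixed-direction example: X versus Y weight 2.5 to 4, Y versus adult weight 0.25 to 0.40, product 0.625 to 1.6. The direct band of 60 to 75 is a weight of 1.33 to 1.67. They overlap, so consistent.

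For banded answers an exactly transitive respondent cannot fail this rule, because the true value lies in both intervals.

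**The case against.** The formula sentence is one slip against three correct statements, and section 2.3.11 opens by defining transitivity correctly. A reader might infer that the test as a whole is built on the wrong product. The documents do not support that: the intended chain is plain, and the X-versus-Y question is asked in order to form it. This stands.

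A reader might also infer that the group-size scale makes transitive respondents fail. The 25-against-50 example depends on the printed product. Under Table 1, same-direction transitive respondents never fail, and the mixed-direction failures come from banding. That stands too, although the non-monotone age pattern described in section 2.3.7 makes mixed-direction answers plausible.

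It is tempting to say that always-choose-younger respondents are certified as consistent when they are not. Table 2 calls their answer undefined below 1, and 0.5 is a convention. Their chained interval (below 0.01) lies inside the direct one (below 1), so they are untestable rather than shown intransitive. They are also reported separately as extreme preferences (section 2.7.3). The 200-fold figure shows how the rule behaves and is not evidence about these people.

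Group size is also the elicited scale and, divided by 100, the scale of the ratio of means, so a 20-person tolerance is not arbitrary. The plan adds a scatter plot, a reversal criterion and a promise of other thresholds. These soften the rule but do not remove the pattern at g = 5.5 to 67.5: the scatter plot does not classify anyone, no reversal occurs, and step 3 shows that moving the cut-off does not help.

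Finally, a simple fold rule on mid-points would be worse in one respect. True sizes of 80, 12 and 9.6 are exactly transitive but are banded to 82.5, 17.5 and 5.5. The prediction is then 14.4 against 5.5, or 2.6-fold. In a simulation of same-direction transitive respondents (uniform 1 to 100, unforced bands, below-1 answers removed), a 1.5-fold rule failed about 20% and a 2-fold rule about 8%. This stands and shapes the fix.

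**Conclusion.** The point holds in two limited parts. The formula sentence in section 2.3.11 is wrong and contradicts three other statements of the same test. The 20-person rule is uneven: for repeated pro-younger answers it passes 4- to 200-fold departures from multiplicativity and fails departures of about 3- to 1.5-fold, so passing partly tracks strength of preference.

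The table in step 2 rests only on Table 2 and the stated rule. How many real respondents answer this way is not known from the documents, and the simulated shares depend on uniform draws.

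The consequence is confined to the Aim 4 pass rate and an exploratory logit. No exclusion depends on the test, and the ratio of means and median of individual ratios do not use it. A reader might infer that the age weights are compromised, but nothing in the documents supports that. Severity is minor to moderate.

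**What to change.** - Correct the formula sentence in section 2.3.11 to (youngest versus middle age) × (middle age versus adult), as in Table 1.
- In section 2.7.3, class a respondent as consistent if the interval obtained by multiplying the bounds of the two chained answers overlaps the interval of the direct answer. Treat exact equivalence answers as points with a small stated tolerance, and state whether intervals that only touch count as overlapping (this decides g = 5.5, where 0.01 to 1 meets 1 to 10).
- Keep the 20-person rule as a sensitivity analysis.
- Report respondents at the below-1 bound in any of the three questions separately as not assessable, and leave them out of the logit.
- Do not apply a fixed-fold rule to the mid-points.

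The cost is one corrected sentence and a change to the classification code, with no new data. The downsides are that some respondents become not assessable and that the overlap rule is lenient where answer bands are wide.
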